### Integrated analysis

Advanced data integration and pathway analysis using systems biology data modelling to investigate integrated mechanistic pathways and reveal novel interactions between different biological modalities will be employed
^
75
^. Cross-validated multivariate models predicting the outcomes or measures of interest will be derived from the full dataset using a gradient-boosted tree algorithm (XGBoost)
^
76
^. A two-layer repeated cross-validation scheme will be used to prevent overfitting, optimize the parameters of the model, and get an estimate of the performance of the model on unseen patients. In brief, patients will be randomly and evenly split into a training set and a test set. An XGBoost model will be trained on the training set and then used to make predictions for the patients in the test set. This procedure will be performed 50 times using different and random train and test splits in each iteration. Final test predictions for each patient will be generated by integrating the model’s predictions for the patient using only the predictions from iterations in which the relevant patient was in the test set. Classifier model performance will be assessed with the area under the receiver operating characteristic curve (AUROC) and the area under the precision-recall curve (AUPRC)
^
77
^. Regression model performance will be assessed using Pearson’s correlation coefficient (Pearson’s R).

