## Introduction

In 2019, an estimated 5.2 million children under five years died worldwide, predominantly in sub-Saharan and South Asia and mainly due to infectious causes
^
1,
2
^. When children in low- and middle-income countries (LMIC) experience an acute illness, their average mortality risk during and after a hospitalisation event remains unacceptably high and can exceed 20%
^
3–
11
^. This high mortality risk may be due to illness severity, underlying comorbidities such as malnutrition, limited healthcare access and resources, and poverty. The results of the CHAIN cohort, as well as other studies, suggest that half of all mortality in children admitted for acute illness in these settings occurs after discharge
^
5,
11,
12
^ but a large group of children can be identified as low risk. In the past decade, very few novel biological interventions have demonstrated the ability to reduce mortality among children in LMIC with acute illnesses
^
13,
14
^. Interventions that have been tested in clinical trials have often been translated from high-income settings rather than being based on a thorough mechanistic understanding of child mortality in LMICs. Finally, typical interventions commonly do not address the multiple biological factors that contribute to acute and post-discharge mortality such as the inciting illness, nutrient deficiencies and other comorbidities including enteropathy and intestinal dysbiosis (
Box 1). These observations highlight the need for an improved understanding of the mechanisms leading to death and for the development of new interventions for prevention of morbidity and mortality.

Box 1. Multiple and Interconnected biological pathways lead to mortality
**
*Infection*
**
Acutely ill children in LMICs typically present with respiratory infection, diarrhoea or encephalopathy and across these syndromes, those with undernutrition are at higher risk of mortality. While deaths are typically associated with these infectious syndromes, positive bacterial blood cultures are found in only <10% of cases
^
15,
16
^. Studies including The Global Enteric Multicenter Study (GEMs) and The Pneumonia Etiology Research for Child Health (PERCH) have identified epidemiological associations between molecular evidence of specific bacterial and viral pathogens and mortality
^
17,
18
^. However, the pathways to mortality during such infections, other than via overwhelming sepsis, are unclear.
**
*Systemic inflammation and altered metabolism*
**

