### Participant enrolment and data collection

The objectives of the CHAIN cohort study, participating sites, patient and public involvement, eligibility, screening, enrolment and follow-up procedures, and specimen collection have been detailed previously
^
57
^. Briefly, 3101 acutely ill children were recruited from nine sites in six countries in sub-Saharan Africa and South Asia. Children were enrolled at admission to hospital and followed up for 180 days after discharge from hospital. Participating sites included rural and urban hospitals in Bangladesh (icddr,b Dhaka Hospital and Matlab Hospital), Burkina Faso (Banfora Regional Referral Hospital), Kenya (Kilifi County Hospital, Mbagathi Sub-County Hospital and Migori County Referral Hospital), Malawi (Queen Elizabeth Central Hospital), Pakistan (Civil Hospital, Karachi), and Uganda (Mulago Hospital). The mid-upper arm circumference (MUAC) was used to enrol children into three strata that included not wasted (MUAC ≥12.5cm for age ≥six months or MUAC ≥12cm for age <six months), moderately wasted (MUAC 11.5 to <12.5 cm for age ≥six months or MUAC 11 to <12 cm for age <six months), and severely wasted or kwashiorkor (oedematous malnutrition) (MUAC <11.5cm for age ≥six months or MUAC <11cm for age <six months or bilateral pedal oedema unexplained by other medical causes). In addition, children in the same communities as hospitalised cases who were not acutely ill: community participants (CP, N=1140) were recruited at a single time-point to establish community norms for demographic and biological factors. Community children
^
57
^ were included into the study if they had no hospital admission in the 14 days prior to contact with the study team and were not ill and therefore are considered to be well and typical for the community rather than ‘healthy’. These community children were from the same neighbourhoods as acutely ill children and therefore, may have had anthropometric deficits, micronutrient deficiencies, helminth infections among others and therefore would not be regarded as 'healthy'.

CHAIN
^
12
^ focused on describing the upstream biomedical and social pathways underlying vulnerability since these may be amenable to interventions at an earlier timepoint and not on the immediate causes of death which is an objective of the Child Health and Mortality Prevention Surveillance (CHAMPS)
^
2

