### Study design

A nested case-cohort design drawing from a larger cohort provides estimates that are representative of the entire cohort while also yielding slightly more statistical power than a case control design
^
58
^. Case-cohort selection involves a random subsample of the original cohort (sub-cohort), independently of how cases are defined, followed by additional inclusion of all cases outside the sub-cohort creating the case-cohort set
^
59
^. This results in overrepresentation of the cases in the case-cohort set compared to the original cohort which is dealt with in analysis by weighting. A further advantage of this design over a case-control design is that the sub-cohort can also be used in analysis of other outcomes. In CHAIN, this could include outcomes of readmission or growth among survivors in future analyses, as well comparisons between acutely ill children and community children and between nutritional strata among acutely ill children in the current analysis.

The original CHAIN cohort stratification was maintained in the CNCC design; thus, a random 24% sub-cohort of children enrolled in the CHAIN cohort stratified by site was selected. This included 658 survivors (sub-cohort non-cases) and 109 deaths (sub-cohort cases). Thereafter, all remaining deaths (n=241 cases) that were not selected in the random 24% sub-cohort (
Figure 3) were added, giving a total of 350 cases. An additional 30 randomly selected community participants from each site (total N=270) were chosen.

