### Sample size

Multiple studies in both low- and high-income settings indicate a prolonged increased mortality risk after admission (including >1 year) compared to the community peers
^
10,
43,
60
^ which is now considered a well-recognised phenomenon. The primary analyses will be of acute mortality occurring within 30-days from admission and post-discharge mortality within 180-days from discharge using samples collected at admission and discharge timepoints. Power and effect size are a function of the number of cases, correlation between cases and survivors, and the ratio of cases to survivors. It is likely that the strength of association between exposures of interests and death will vary in magnitude between the 30-day and 180-day mortality periods. Sample size calculations suggest that a ratio of one case to two non-cases is adequate to reliably detect an HR of 1.5 at >80% power. The design selected all available deaths and simulation-based power calculations suggested that adding more non-cases per cases would yield minimal gains in power while incurring substantial additional expense.

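### The set was sampled on death at any time, but the 30-day mortality analyses state neither a non-case group nor sampling-fraction weights

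*Protocol article*

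**What the plan says.** All references are to the protocol article.

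- **Sampling (Study design).** "a random 24% sub-cohort of children enrolled in the CHAIN cohort stratified by site was selected". On its composition: "This included 658 survivors (sub-cohort non-cases) and 109 deaths (sub-cohort cases". To this were added "all remaining deaths (n=241 cases) that were not selected in the random 24% sub-cohort", which makes 350 cases. Case status here means death at any time in the study.
- **Endpoints (Sample size).** The primary analyses are of "acute mortality occurring within 30-days from admission and post-discharge mortality within 180-days from discharge".
- **Weighting (Study design).** The design is said to produce "overrepresentation of the cases in the case-cohort set compared to the original cohort which is dealt with in analysis by weighting". No scheme is given, and it is not tied to either endpoint.
- **Weighting (Statistical analysis).** Weights are named once, for the case fatality rates of the targeted assays. The Wilcoxon test and Hedges' g in the same section carry none.
- **Models (Integrated analysis; Stacked generalization).** "Cross-validated multivariate models predicting the outcomes or measures of interest will be derived from the full dataset". Neither these models, nor their AUROC and AUPRC, nor the meta-learner is given weights.

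No section says which children are the non-cases for 30-day mortality.

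**The concern.** For a binary 30-day outcome, a child who dies on day 60 is a non-case. That child was nevertheless sampled with certainty, while a child who survived had about a one in four chance of selection. The 30-day non-case group would therefore mix two kinds of children at very different sampling fractions.

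AUROC is not affected by taking all of the true cases. It is affected by uneven sampling inside the non-case group, and so are the rank test and the standardised mean difference. On any feature where later deaths sit between survivors and early deaths, an over-supply of later deaths makes early deaths look less distinctive than they are in the cohort.

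Using only end-of-study survivors as comparators avoids that mixture, but it chooses 30-day non-cases by what happens to them after day 30. Neither route gives the cohort-representative estimates for which the case-cohort design was chosen. At stake is one of the two primary endpoints.

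**Working it through.** **The plan's own counts.** The cohort is given as "3101 acutely ill children were recruited from nine sites in six countries".

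- Sub-cohort: 658 + 109 = 767, and 767/3101 = 24.7%.
- All cases: 109 + 241 = 350.
- Whole set with community children: 350 + 658 + 270 = 1278, as stated.
- Survivors in the cohort: 3101 − 350 = 2751, taking the 350 as all cohort deaths. The realised fraction is 658/2751 = 23.9%, so the overall survivor weight is 2751/658 = 4.18. The weight for every death is 1.

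**Number of later deaths, L.** The article does not give it. The nearest guide is the statement that "half of all mortality in children admitted for acute illness in these settings occurs after discharge", and death after discharge is not the same as death after day 30. I assume 20% to 80% of 350, that is L = 70 to 280, with L = 175 as the central value.

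**Share of later deaths among 30-day non-cases.** In the set this is L/(658 + L); in the cohort it is L/(2751 + L).

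| L | Set, unweighted | Cohort | Ratio |
|---|---|---|---|
| 70 | 70/728 = 9.6% | 70/2821 = 2.5% | 3.88 |
| 105 | 105/763 = 13.8% | 105/2856 = 3.7% | 3.74 |
| 175 | 175/833 = 21.0% | 175/2926 = 6.0% | 3.51 |
| 210 | 210/868 = 24.2% | 210/2961 = 7.1% | 3.41 |
| 280 | 280/938 = 29.9% | 280/3031 = 9.2% | 3.23 |

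The ratio hardly depends on L.

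**Effect on AUROC.** With w the share above, AUROC = w × AUC(early v later deaths) + (1 − w) × AUC(early deaths v survivors). I assume a normal marker with equal variances, AUC(early v survivors) = 0.80 and L = 175. If later deaths lie midway, AUC(early v later) = Φ(0.8416/2) = 0.663.

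- Cohort: 0.060 × 0.663 + 0.940 × 0.80 = 0.792.
- Set, unweighted: 0.210 × 0.663 + 0.790 × 0.80 = 0.771.
- Shift: −0.021. Hedges' g falls from 1.14 to 1.04.

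A simulation of 1000 data sets under the same assumptions gave 0.791 for the cohort, 0.771 for the unweighted set, 0.791 with survivors weighted by 4.18, and 0.800 for survivors-only comparators.

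**Dependence on where later deaths lie** (L = 175, AUC 0.80):

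| Position of later deaths | AUROC shift |
|---|---|
| Slightly beyond survivors, away from early deaths | +0.008 |
| Same as survivors | 0.000 |
| A quarter of the way to early deaths | −0.010 |
| Midway | −0.021 |
| Same as early deaths | −0.045 |

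For AUC 0.70 to 0.90 and L = 105 to 210, the midway shift runs from −0.010 to −0.028. The largest fall on that grid is −0.068 (AUC 0.90, L = 210, later deaths identical to early deaths).

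**Which weights correct it.** A single weight k for all 30-day non-cases leaves the share at 175k/(175k + 658k) = 21.0%. Weights by sampling fraction give 175/(175 + 4.18 × 658) = 6.0%, the cohort value.

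**The case against.** Much can be said on the other side.

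1. **Weighting is promised.** Study design commits to it in general terms, and correct weights remove the shift completely. This stands in part. The promise concerns over-representation of cases, whereas the difficulty here lies inside the non-cases. Weights that follow 30-day case status would honour the promise and correct nothing. The analysis sections then name weights for one descriptive quantity only, and the Wilcoxon test and Hedges' g are unweighted as ordinarily computed.
2. **Later deaths may not be among the non-cases.** Study design labels the 658 survivors as non-cases, and Sample size speaks of a ratio of cases to survivors. This stands: no section puts later deaths in the 30-day comparator. But the label describes the draw, and a survivors-only comparator selects on later survival.
3. **The full dataset may mean all modalities.** This also stands. Stacked generalization contrasts it with single-modality models, so the phrase does not settle who is in the 30-day analysis.
4. **The detail may be in a fuller plan.** An article need not give weight formulae. But these analyses, run as the article describes them, miss the cohort value under either comparator, so this is more than a missing formula.

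A reader might infer that 30-day results will be biased towards the null. The article does not support that. It requires later deaths to be counted as non-cases without proper weights and to lie between survivors and early deaths on the feature. The article gives no data on the last condition, and expects the strength of association to differ between the two periods.

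**Conclusion.** The point holds in a conditional form. One set sampled on any death serves two primary endpoints, and the 30-day tests, effect sizes and models are stated without a non-case group or sampling-fraction weights.

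- If later deaths are unweighted non-cases, they are over-represented about 3.2 to 3.9 times (L = 70 to 280 assumed).
- The resulting shift is modest: about 0.01 to 0.03 in AUROC when later deaths lie midway, larger if they resemble early deaths, and nil or reversed for other features.
- If only survivors are used, the shift is smaller and in the other direction (about 0.80 against 0.79).

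These sizes rest on the assumed number of later deaths, a normal marker and the assumed AUROC values. The post-discharge endpoint does not share the problem, because its non-cases are survivors. The change should be made because it concerns a primary endpoint and needs no new samples.

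**What to change.** State for 30-day mortality that non-cases are all children alive at day 30, including those who die later. Apply inverse realised sampling-fraction weights by site in the effect sizes, tests, model training and AUROC/AUPRC: 1 for every death and about 4.18 overall for survivors. Site-level fractions are not in the article and must come from the sampling records. Say explicitly that weights follow the actual probability of selection, not case status for the endpoint being analysed.

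Alternatively, restrict 30-day non-cases to sub-cohort members alive at day 30, keeping those who die later and leaving out later deaths that entered only as added cases. Realised fractions still matter here, because the sub-cohort holds 109/350 = 31.1% of deaths against 23.9% of survivors. If half of the 109 are later deaths, their unweighted share is 54.5/712.5 = 7.6% against 6.0% in the cohort, a much smaller excess.

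The cost of the first option is some extra analysis work, including a weighted version of the rank test, and some loss of precision. The cost of the second is that added later deaths leave the 30-day comparison, where they are not cases.

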### Stacked generalization

To account for the differing information content between biological modalities and allow each modality to participate equally in the predictive models for the outcomes of interest, a stacked generalization approach will be employed
^
75
^. An independent predictive model will be trained using only the data from each modality while maintaining the same cross-validation folds across all modalities. A meta-learner will be subsequently trained to combine the predictions from each independent biological modality. Ultimately, each modality’s predictive model and the global meta-learner will be used to generate the final cross-validated test predictions for each patient in the dataset.

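### Mortality models are validated only on random patient splits pooled over nine sites, so the AUROC can include between-site differences; add within-site, site-only and leave-one-site-out figures

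*Protocol article*

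**What the plan says.** Under Integrated analysis, the Protocol article fixes the validation unit as the patient: "patients will be randomly and evenly split into a training set and a test set". It adds: "This procedure will be performed 50 times using different and random train and test splits in each iteration". Each child's test predictions are combined over the iterations in which that child was in the test half, and classifiers are then assessed by AUROC and AUPRC. The declared purpose is to "get an estimate of the performance of the model on unseen patients".

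Under Stacked generalization, one model is trained per modality while "maintaining the same cross-validation folds across all modalities", and a meta-learner combines the modality predictions.

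On the population, the article says that "3101 acutely ill children were recruited from nine sites in six countries in sub-Saharan Africa and South Asia". Site is treated as important elsewhere: "a random 24% sub-cohort of children enrolled in the CHAIN cohort stratified by site was selected", and site is listed among the participant characteristics to be used.

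Under Statistical analysis, each feature is to be regressed linearly on confounders and the residuals kept as adjusted features. The confounders are not named, and the text does not say whether these residuals are the inputs to XGBoost.

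**The concern.** The study wants to learn how biology leads to death, in order to inform interventions. Several modalities could plausibly identify where a child lives: the stool metagenome, enteric pathogens, aflatoxin and haemoglobin variants. If sites also differ in mortality, a tree model can gain discrimination by recognising the site, even when site is not offered as a predictor. A random patient split cannot expose this, because each test child comes from a site whose death rate was already seen in training. A single AUROC pooled over sites counts between-site pairs (a death at one site against a survivor at another) together with within-site pairs. Without a within-site figure or a benchmark, a reader could not tell how much of an AUROC of, say, 0.65 reflects biology and how much reflects location.

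**Working it through.** **Inputs from the article.** Study design: 109 + 241 = 350 deaths and 658 survivors, so 350 + 658 = 1008 hospitalised children; adding 270 community children gives the stated 1278. The parent cohort is 3101, so overall mortality is 350/3101 = 11.3%. Survivors are sampled at 658/(3101 − 350) = 658/2751 = 23.9%, which agrees with the stated 24%. There are nine sites. Site-specific mortality is not given and is assumed below.

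**Step 1: is every site in both halves?** The average is 1008/9 = 112 children per site. The chance that a site of n children falls wholly in one half is about 2 × 0.5^n: about 4 × 10⁻³⁴ for n = 112, and 2 × 10⁻⁶ even for n = 20. It is effectively certain that every site is in both.

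**Step 2: AUROC from site identity alone.** Assume nine equal sites with mortality r₁ < … < r₉, linearly spaced over a range R and averaging r̄ = 0.1129. Then

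AUROC = 0.5 + Σ_{i>j}(rᵢ − rⱼ) / [2 × 9² × r̄(1 − r̄)].

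For linear spacing the sum is (R/8) × 120 = 15R. The denominator is 162 × 0.1129 × 0.8871 = 16.22. So AUROC ≈ 0.5 + 0.925R. The ranges below average 11.5%, so R is scaled by 0.1129/0.115 = 0.98.

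| Assumed site mortality | R after scaling | Site-only AUROC |
|---|---|---|
| Equal | 0 | 0.50 |
| 8–15% | 0.069 | 0.56 |
| 5–18% | 0.128 | 0.62 |
| 3–20% | 0.167 | 0.65 |

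The case enrichment does not alter these values. All deaths are taken, and survivors are sampled at about the same fraction at each site.

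**Step 3: site added to a real signal.** With score = site logit + 0.5x and a within-site AUROC of Φ(0.5/√2) = 0.64, simulation gives a pooled AUROC of 0.65, 0.68 and 0.71 for the last three rows. Like step 2, this assumes that site risk is known perfectly.

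**Step 4: when site must be learned from the features.** An illustrative simulation used ridge regression in place of XGBoost, with 200 features, an assumed site shift of SD 0.5, ten random half-splits per dataset and 15 datasets. The weak signal was a 0.2 SD shift in ten features.

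| Biological signal | Site mortality | Pooled, random split | Within site, random split | Within site, leave-one-site-out |
|---|---|---|---|---|
| None | equal | 0.51 | 0.50 | 0.51 |
| None | 6–17% | 0.53 | 0.49 | 0.50 |
| None | 2–21% | 0.59 | 0.49 | 0.50 |
| Weak | equal | 0.60 | 0.59 | 0.60 |
| Weak | 6–17% | 0.60 | 0.57 | 0.59 |
| Weak | 2–21% | 0.66 | 0.58 | 0.59 |

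The site-only values for 6–17% and 2–21% are 0.60 and 0.67, so the learned gain (0.53 and 0.59 with no signal) is well below the ceiling. Residualising the features on site removed the inflation (pooled 0.47–0.51 with no signal).

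**The case against.** The strongest reply is that the scheme does what it says. Its declared target is unseen patients, not unseen sites, and a random patient split is sound internal validation for that target. This stands. Replacing it with leave-one-site-out as the headline would change the quantity estimated, not repair an error.

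Second, a reader might infer that the reported AUROC will overstate biological prediction. The article does not support that. Inflation needs three things together: unequal site mortality, features that carry site information, and no adjustment for site. The first is not reported. The third is left open by the planned residuals, whose confounder list a condensed article may reasonably leave to the full plan. With equal mortality the inflation is zero.

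Three further inferences should also be resisted:

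- Handling differences between sites are not shown. The article reports harmonised procedures and training, and gives freezing and storage times only for all sites together.
- Reusing the same folds across modalities does not in itself favour modalities that encode site. It only keeps each child's test status aligned. Any advantage would come from the features.
- The article describes no feature ranking from XGBoost. Pathway enrichment starts from genes and proteins significantly associated with outcome, and the cross-validation split does not alter association tests.

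The reply does not remove the core point. The validation is stated in some detail, the residuals are not linked to the models, and the only discrimination summary described is taken over all sites together.

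**Conclusion.** This is a worthwhile and cheap improvement, not a mistake in the plan. As described, the AUROC supports a statement about new patients at these nine sites. It does not support a statement about prediction within a site or at a new site.

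The possible size depends on site mortality that the article does not give. Assuming equal-sized sites and linearly spread rates, site identity alone is worth an AUROC of 0.50 (no spread) to about 0.65 (3–20%). For each spread that is an upper bound on what site can give a model with no within-site signal. When site had to be learned from simulated features, the pooled AUROC exceeded the leave-one-site-out within-site value by between nothing and 0.09 (0.59 against 0.50 in the widest spread with no signal; 0.66 against 0.59 with a weak signal). Those figures also depend on the assumed site shift and on ridge regression in place of XGBoost.

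**What to change.** Keep the 50 random splits and the pooled AUROC. Report beside it:

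1. the AUROC computed within each site and averaged with weights proportional to deaths;
2. a benchmark AUROC from a model that uses site alone;
3. leave-one-site-out cross-validation as a sensitivity analysis (train on eight sites, test on the ninth), with the same folds for every modality and the meta-learner, and the AUROC computed within the held-out site before averaging.

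State whether site is among the confounders regressed out and whether the residuals feed XGBoost. If they do, fit the residualisation within training folds. A held-out site has no coefficient from training, so say how it is handled in item 3.

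The cost is wording and computing on data already held. The AUROC will probably be lower, and single-site values will be imprecise. There are about 350/9 = 39 deaths and 658/9 = 73 survivors per site on average. By the Hanley–McNeil formula at an AUROC of 0.60, the standard error for one site is √[(0.24 + 38 × 0.0686 + 72 × 0.09)/(39 × 73)] = 0.057. If about half the deaths fall in each mortality period (19 per site), it is √[(0.24 + 18 × 0.0686 + 72 × 0.09)/(19 × 73)] = 0.076. Hence the weighted average should be reported, not nine separate claims.
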